## Abstract

**Introduction:**

Multiparametric MRI (mpMRI) is now widely used to risk stratify men with a suspicion of prostate cancer and identify suspicious regions for biopsy. However, the technique has modest specificity and a high false-positive rate, especially in men with mpMRI scored as indeterminate (3/5) or likely (4/5) to have clinically significant cancer (csPCa) (Gleason ≥3+4). Advanced MRI techniques have emerged which seek to improve this characterisation and could predict biopsy results non-invasively. Before these techniques are translated clinically, robust histological and clinical validation is required.

**Methods and analysis:**

This study aims to clinically validate two advanced MRI techniques in a prospectively recruited cohort of men suspected of prostate cancer. Histological analysis of men undergoing biopsy or prostatectomy will be used for biological validation of biomarkers derived from Vascular and Extracellular Restricted Diffusion for Cytometry in Tumours and Luminal Water imaging. In particular, prostatectomy specimens will be processed using three-dimension printed patient-specific moulds to allow for accurate MRI and histology mapping. The index tests will be compared with the histological reference standard to derive false positive rate and true positive rate for men with mpMRI scores which are indeterminate (3/5) or likely (4/5) to have clinically significant prostate cancer (csPCa). Histopathological validation from both biopsy and prostatectomy samples will provide the best ground truth in validating promising MRI techniques which could predict biopsy results and help avoid unnecessary biopsies in men suspected of prostate cancer.

**Ethics and dissemination:**

Ethical approval was granted by the London—Queen Square Research Ethics Committee (19/LO/1803) on 23 January 2020. Results from the study will be presented at conferences and submitted to peer-reviewed journals for publication. Results will also be available on ClinicalTrials.gov.

**Trial registration number:**

NCT04792138.

Strengths and limitations of this studyA prospective cohort of men suspected of prostate cancer referred to two tertiary care centres in the UK representative of the population of interest.The reference standard to validate novel imaging biomarkers includes both targeted biopsy and matched whole-mount prostatectomy histology without participants deviating from standard clinical care.The patient-specific specimen handling protocol for prostatectomy which was developed at this institution allows for accurate matching of MRI and histology.This protocol will produce a rich imaging and histology dataset that can be used to train machine learning algorithms and validate novel imaging biomarkers.Novel imaging biomarkers will not influence clinical decisions, which is ethically sound for novel imaging biomarkers which have not been validated clinically.

Histological validation from biopsy alone has limitations of only validating small regions of the prostate. In contrast, histological validation from prostatectomy specimens leads to a selection bias where men with abnormal prostates are selected rather than those men who may have indolent or benign diseases. Furthermore, the prostate can be sliced in a different axis in histopathology compared with imaging which causes imperfect matching and poor validation. A patient-specific specimen handling for prostatectomy specimens can overcome these limitations and allow better matching of MRI and whole-mount histopathology.^13^

In this study, both biopsy and MRI matched whole-mount histology from prostatectomy will be used for clinical validation of novel MRI techniques in a prospective cohort of men suspected of prostate cancer. In particular, the impact of index tests on the false positive rate in men who are scored Likert 3 or 4 and underwent biopsy or prostatectomy will be evaluated. The decision to biopsy or recommendation for prostatectomy will not be influenced by the novel MRI techniques being validated.

## Methods and analysis

### Study Design

Histo-MRI is an observational, prospective, cohort study recruiting men with clinical suspicion of prostate cancer from two centres: University College London Hospital (UCLH) and Barts Health. The index tests (VERDICT MRI and LWI) and standard of care mpMRI will be performed at one centralised centre (UCLH). The study opened for recruitment in October 2020 and the anticipated study end date is October 2023. Participants will undergo the both tests before undergoing biopsy if indicated by the standard test. The index tests will not be used to select patients for biopsy. If a recruited participant is diagnosed with prostate cancer and chooses to undergo prostatectomy, the prostate specimen will undergo a specific specimen handling protocol designed to align histopathology to MRI (figure 1).

**Figure 1 F1:**
[figure not shown]
Protocol for matching MRI to Whole mount histology. The participant’s prostate is contoured by a radiologist on preoperative imaging (‘in vivo MRI’) slice by slice. Based on these contours, a mould specific to the participant’s prostate is 3D printed. The ‘reference slice’ is predefined based on the location of the tumour. After prostatectomy, the prostate is scanned in the mould (‘ex-vivo MRI’). The prostate is sectioned first at the predefined reference slice. The remainder of the prostate is then sliced as standard. Stained ‘whole Mount histology’ is then matched with ex vivo and in vivo imaging. 3D, three dimensions.

The primary objective is to assess whether the index tests can reduce false positives from mpMRI by 20% for men undergoing biopsy or biopsy and prostatectomy. Clinically significant prostate cancer (csPCa) for biopsies is defined as any single biopsy core containing Gleason grade 3+4 or above. For prostatectomy, csPCa is defined as the predominant grade of 3+4 or above in the same matched region on whole mount histology as the abnormality on MRI.

The secondary objectives will examine the proportions of true positive lesions from the index tests.

Exploratory analyses will determine the correlation of VERDICT and LWI parameters to histological parameters. For VERDCIT MRI: fractional intracellular fraction (FIC) to fractional histological intracellular component, fractional extracellular extravascular space to histological glandular and stromal component and fractional vascular volume (FVASC) to histological vascular component. For LWI, luminal water fraction (LWF) will be correlated to luminal space fraction.

Matched MR and histology images will be used as training data for machine learning algorithms. The algorithms will be used to solve a variety of regression problems where the input is MRI and the output is the histological features in each voxel or the full histological image appearance itself, building on previous work from our group.^14–16^

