### Data analysis

Reporting of clinical mpMRI will follow standard of care and be reported by Uro-radiologists based at UCLH on an ordinal Likert scale (1–5): 1—tumour highly unlikely, 2—tumour unlikely, 3—equivocal, 4—tumour likely and 5—tumour highly likely. If the mpMRI study is reported as Likert three or four and the patient is offered a biopsy, a radiologist (blinded to biopsy results/histopathology) will use the pictorial report to derive index test quantitative parameters: FIC for VERDICT MRI and LWF from LWI. Thresholds of index test parameters based on previous work from the INNOVATE trial will be applied to determine whether a lesion is positive or negative.^7^ This will be compared with a histological reference standard allowing assessment of false positive rate, sensitivity and specificity.

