### Statistical analyses

A sample size of 128 subjects achieves a 90% power to detect a difference of 20% in the proportion of false positives between the index tests (0.45) and standard test (0.65). This calculation uses a two-sided Pearson χ^2^ test with a significance level of 0.05 and confidence level of 95%. We anticipate a biopsy rate of 57% in the cohort and of those biopsied, 75% to be scored Likert 3 or 4, based on results from the recent INNOVATE trial at our institution.^7^ Therefore, a sample size of 300 will provide sufficient power, with an estimated 171 men predicted to have biopsy and of these men, 128 to have a Likert score of 3 or 4.

Approximately 800 patients undergo prostatectomy per year at UCLH and 150 are referred from Barts Health National Health Service(NHS) trust. We estimate in a sample size of 300, approximately 50 patients will elect to have a prostatectomy based on clinical experience and recruitment in other studies carried out at our institution.

The difference in proportion of false positives and true positives for the index test will be compared with the standard test (mpMRI) using a χ^2^ test. Correlation coefficients will be used to determine the correlation between index test parameters and histological measures.

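### The primary objective and sample size treat VERDICT and LWI as one result, so the stated 90% power at 5% belongs to a comparison the text does not identify

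*Protocol article*

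**What the plan says.** All references are to the protocol article, Methods and analysis.

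- **Study Design** names two index tests, VERDICT MRI and LWI. The primary objective, below Figure 1 in that section, covers them together: "The primary objective is to assess whether the index tests can reduce false positives from mpMRI by 20" per cent. The proportion of true positive lesions is a secondary objective.
- **Data analysis** has a radiologist "derive index test quantitative parameters: FIC for VERDICT MRI and LWF from LWI" for Likert 3 or 4 studies where a biopsy is offered. Thresholds from an earlier trial "will be applied to determine whether a lesion is positive or negative". No rule is given for a lesion that FIC calls positive and LWF calls negative, or the reverse.
- **Statistical analyses** states "A sample size of 128 subjects achieves a 90% power to detect a difference of 20" per cent, with one pair of rates ("between the index tests (0.45) and standard test (0.65"), a two-sided Pearson chi-square test and a significance level of 0.05. The paragraph on the planned comparison then moves to the singular and compares one index test with mpMRI, without saying which.

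**The concern.** Two tests with separate thresholds give two results per lesion and two false-positive proportions. A single objective, a single 0.45 and a single 0.05 describe one comparison. At least four rules fit the wording: one named test succeeds, either succeeds, both succeed, or a combined reading succeeds. They differ in error rate and in power, so the stated 90% at 5% cannot be attached to the primary objective until one is chosen.

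The choice also affects what is being measured. Lesions positive on both FIC and LWF are a subset of those positive on either parameter. A rule adopted afterwards that requires both to be positive can therefore only lower the number of false positives or leave it unchanged. The same holds for detected cancers. Because true positives are a secondary objective, the primary result would not register that loss, although the Introduction describes the need as fewer false positives without missing significant cancer.

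**Working it through.** **Inputs.** From Statistical analyses: proportions 0.65 and 0.45, two-sided alpha 0.05, power 90%, n = 128, biopsy rate 57%, Likert 3 or 4 share 75%, 300 recruited. The correlation between the two test results is not in the article, so a range is assumed.

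**1. The plan's own figure.** With pooled variance under the null and mean proportion 0.55:

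n = [1.960 × √(2 × 0.55 × 0.45) + 1.282 × √(0.65 × 0.35 + 0.45 × 0.55)]² / 0.20²
= [1.379 + 0.883]² / 0.04 = 127.9, rounded up to **128**; power at 128 is 90.0%.

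Recruitment: 300 × 0.57 = 171, and 171 × 0.75 = 128. Both figures reproduce, for one comparison at the full 0.05. In this formula 128 is a per-group number for independent groups. Whether that suits men who receive all the tests is a separate question; the steps below stay on the plan's own basis.

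**2. Either test may carry the claim, each at two-sided 0.05.** If independent, the chance of at least one rejection is 1 − 0.95² = 9.75%. Counting only rejections that favour the index test (0.025 each), it is 1 − 0.975² = 4.94%, against 2.5% for a single test. With correlated test statistics (bivariate normal):

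| Assumed correlation | Any rejection | Favourable direction only |
|---|---|---|
| 0 | 9.75% | 4.9% |
| 0.3 | 9.5% | 4.8% |
| 0.5 | 9.1% | 4.5% |
| 0.8 | 7.8% | 3.9% |
| 0.9 | 7.0% | 3.5% |

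The stated two-sided 5% is reached only if the two tests agree perfectly.

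**3. Both tests must succeed, each at 0.05.** No alpha split is needed, but power falls. If each test truly has 0.45, joint power at n = 128 is 0.900² = 81% if independent, 83% at correlation 0.5 and 86% at 0.8.

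**4. Either may win, alpha split 0.025 + 0.025.** The critical value becomes 2.241:

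- n = [2.241 × 0.7036 + 0.883]² / 0.04 = 151.3, rounded up to 152. Recruitment would be 152 / (0.57 × 0.75) = 356.
- Keeping n = 128: (0.20 × √128 − 1.577) / 0.689 = 0.995, which is power of 84.0% per test.

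**5. One test or one rule named in advance.** 128 and 300 stand unchanged.

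**The case against.** The strongest reply is that this is loose wording. Each technique has its own parameter and threshold, and the comparison sentence is in the singular, so the natural reading is two separate comparisons with mpMRI. Whether two distinct techniques need joint error control is debatable, more so in an observational validation study whose index tests do not guide biopsy. Multiplicity and discordant results may also be handled in a full protocol or analysis plan that is not shown.

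Much of this stands, and it rules out several stronger inferences that a reader might draw:

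- **That the 5% level fails.** No section states an either-test success rule. If both must win, or one rule is fixed in advance, 5% holds. The text supports only that it is not guaranteed.
- **That there is a 9.75% chance of falsely claiming a reduction.** That figure includes results where the index test is significantly worse than mpMRI. For a wrong claim of reduction, the ceiling for two tests is 4.9%.
- **That a combined rule is planned, with calculable rates.** The article contains none. Numerical false-positive and sensitivity figures for such rules would need assumed sensitivities and independence between two readings of the same lesion. Only the subset argument holds without them.

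There is one further limit. FIC and LWF are read only on lesions mpMRI has already scored 3 or 4. If all tests share that denominator, an index test cannot have more false positives than mpMRI, and a standard chi-square null is only nominal. The error figures therefore take the plan's test at its stated level.

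The reply does not remove the point. The primary objective, effect size, alpha and sample size are fixed in this text, not deferred, and they are fixed for an unidentified quantity. Even on the natural reading of two comparisons, the article does not say what meets the primary objective.

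**Conclusion.** The point holds as a specification fault with a conditional effect on error rate and power. The stated 90% power at 5% is correct for one prespecified comparison, and the text does not name it. If either test may carry the claim, nominal two-sided family-wise error is up to 9.75%, and a wrong claim of reduction rises from 2.5% to at most 4.9%. If both must succeed, joint power is about 81% to 86% rather than 90%. These figures assume the plan's unpaired calculation, a true 0.45 for each test in the power figures, and correlations the article does not supply. The freedom to adopt a combined rule afterwards needs no such numbers: requiring both tests to be positive cannot raise false positives and cannot raise cancer detection. It should be corrected, at small cost.

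**What to change.** Restate the primary objective as two separate comparisons with mpMRI, FIC and LWF each at its prespecified threshold, and choose one of two structures:

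1. **Fixed order.** Name one comparison as primary at two-sided 0.05, and test the other at 0.05 only if the first succeeds. The sponsor sets the order, since nothing in the article ranks the techniques. The 128 and 300 stand for the comparison named as primary. The cost is that the second test cannot be claimed if the first fails. If both truly reach 0.45, the chance of making both claims is the 81% to 86% above.
2. **Split alpha.** Test each at 0.025 and restate power at n = 128 as about 84% per test. Neither claim then depends on the other; keeping 90% would need 152 evaluable men, about 356 recruited.

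In either case, tie the 0.45 to the named test (or give one figure for each), make the singular and plural wording agree across sections, and label any combined FIC/LWF rule exploratory. Option 1, or option 2 at the present sample size, changes wording only and needs no additional men or scans.

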### Participants

Participants will be approached consecutively from Urology clinics at the point of referral from two centres: UCLH Foundation Trust, London, UK and Barts Health, London, UK. Inclusion and exclusion criteria are stated in box 1. Informed consent will be obtained on the day of the index test and participants will be given at least 24 hours before being consented to consider participation.

Box 1Inclusion, exclusion and withdrawal criteriaPatient inclusion criteriaBiopsy naïve men with clinical suspicion of prostate cancer.Patient exclusion criteriaMen unable to have an MRI scan or in whom artifactartefact would reduce quality of MRI.Men unable to given informed consent.Previous treatment of prostate cancer (surgery, radiotherapy, hormone treatment).Previous biopsy.Withdrawal criteriaImages inadequate for analysis.

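### Withdrawing men for inadequate images takes index-test failures out of the primary comparison, so the fall in false positives is larger than in all eligible biopsied men, and the sample size allows for no such loss

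*Protocol article*

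**What the plan says.** Box 1 (Participants) gives a single withdrawal criterion: "Withdrawal criteriaImages inadequate for analysis" (the box label has run into the entry). The same box separately excludes at entry men whose MRI quality would be reduced by artefact, so the withdrawal rule concerns men already enrolled and scanned. It does not say which images count (mpMRI, VERDICT or LWI), or whether failure of one index test removes a man from both comparisons.

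The Study Design section states: "The primary objective is to assess whether the index tests can reduce false positives from mpMRI by 20% for men undergoing biopsy", with or without later prostatectomy. It also says that the index tests play no part in choosing who is biopsied.

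The Data analysis section has FIC and LWF derived by a radiologist who does not know the histology.

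The Statistical analyses section states: "A sample size of 128 subjects achieves a 90% power to detect a difference of 20% in the proportion of false positives". The values assumed are 0.65 for mpMRI and 0.45 for an index test. It then says "We anticipate a biopsy rate of 57% in the cohort and of those biopsied, 75% to be scored Likert 3 or 4", which turns 300 recruits into the required number, "with an estimated 171 men predicted to have biopsy and of these men, 128 to have a Likert score of 3 or 4".

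**The concern.** Biopsy follows from mpMRI alone. A Likert 3 or 4 man with unreadable VERDICT or LWI images therefore still has everything needed to classify his mpMRI result as a true or false positive. What he lacks is an index result that could reclassify him. If the question is how many mpMRI false positives the index test removes among men going to biopsy, he is a man in whom it removed none. Withdrawing him confines the comparison to technically successful scans, and the reported fall then answers a narrower question than the stated objective.

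The protocol also foresees image failure in Box 1 but does not provide for it in the sample size. The stated yield is reached only if no Likert 3 or 4 man who is biopsied is withdrawn.

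**Working it through.** **Inputs from the Statistical analyses section.** False-positive proportions 0.65 (mpMRI) and 0.45 (index test); two-sided Pearson chi-square at 0.05; 90% power; 128 men; 300 recruited; 57% biopsied; 75% of those Likert 3 or 4.

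**Assumed input.** The unreadable fraction u among Likert 3 or 4 biopsied men is not given. I use 5%, 10% and 20%.

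**1. The plan's own figure.** With pooled variance and no continuity correction, mean proportion 0.55:

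n = [1.960 × √(2 × 0.55 × 0.45) + 1.2816 × √(0.65 × 0.35 + 0.45 × 0.55)]² / 0.20² = (1.379 + 0.883)² / 0.04 ≈ 128 per test, with power 90.0%.

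The stated 128 is reproduced as the number of men contributing to each test's proportion. Read as two groups of 64, power would be only 62.6%.

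**2. Slack.** 300 × 0.57 = 171, and 171 × 0.75 = 128.25. Against 128 needed, the margin is 0.25 of a man.

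**3. Effect on the fall.** Let d be the fall in readable men. In unreadable men the index test changes nothing, so their contribution is zero whatever their histology. The fall in all such men is (1-u) × d, and the readable-only figure is larger by 1/(1-u). With d = 0.20:

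- u = 5%: 0.95 × 0.20 = 0.19
- u = 10%: 0.90 × 0.20 = 0.18
- u = 20%: 0.80 × 0.20 = 0.16

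**4. Power on the plan's formula.**

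Power = Φ{[Δ√n − 1.960 × √(2p̄(1−p̄))] / √(p₁(1−p₁) + p₂(1−p₂))}, where Δ = p₁ − p₂ and p̄ is their mean.

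Under withdrawal, p₁ = 0.65, p₂ = 0.45 and n = 128(1-u). With failures kept as index-positive, n = 128 and p₂ = 0.45(1-u) + 0.65u, assuming that failure is unrelated to histology.

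| u | n, withdrawal | Power, withdrawal | p₂, failures kept | Power, failures kept |
|---|---|---|---|---|
| 5% | 121.6 | 88.5% | 0.46 | 86.9% |
| 10% | 115.2 | 86.7% | 0.47 | 83.1% |
| 20% | 102.4 | 82.5% | 0.49 | 73.7% |

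To keep 128 readable men under withdrawal, recruitment would be 128 / (1-u) / 0.4275 (0.57 × 0.75 = 0.4275), which gives 316, 333 and 375.

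**5. How far the power loss is real.** The formula treats the two proportions as independent groups, but both tests are read in the same men. If the index tests only reclassify mpMRI-positive lesions, all discordance runs one way. An exact McNemar test then needs 6 discordant men (2 × 0.5⁶ = 0.031). With 20% discordance, the chance of at least 6 exceeds 99.9% even at 102 men. Failures kept as index-positive are concordant for false positives, so they leave the expected discordant count unchanged: at u = 20%, 128 × 0.16 = 102.4 × 0.20 = 20.48.

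**The case against.** The strongest reply is that this is early validation of preset thresholds, in which the index tests do not guide care. Performance in readable scans is a legitimate target there, and an estimate explicitly confined to such scans need not be biased. That stands as far as it goes, but the stated objective carries no such limit: it is put to men undergoing biopsy.

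The size is also unknown and may be small. The entry exclusion for artefact should reduce later failures, and at 5% the effect is one point in 20. That is accepted. So is the point that handling of unreadable tests is often left to an analysis plan. Here, however, the article fixes a rule, and the rule is withdrawal.

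Three stronger readings are tempting, and the document does not support them.

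- A reader might infer that adequacy can be judged with the histology in view. The Data analysis section blinds the radiologist who derives the index parameters, and that reader is the natural person to find unreadable images. What remains is that Box 1 does not tie the withdrawal decision to that reader.
- A reader might infer that a man with a failed VERDICT scan and a good LWI scan is lost to both comparisons. Box 1 does not say so; it leaves the matter open.
- A reader might infer that the study would be short of men. The power loss belongs to the independent-groups formula, and a paired analysis would have ample power.

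Finally, keeping failures as index-positive lowers power on the plan's formula more than withdrawal does. If carried over to true positives, it would credit a failed test with a detection. Both points are right, and the fix has to deal with them.

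**Conclusion.** The point holds in a limited form. As written, the rule removes index-test failures from the primary comparison, and the reported fall then exceeds the fall in all Likert 3 or 4 biopsied men by 1/(1-u). This rests on two things: the pathway in the protocol, where mpMRI alone leads to biopsy, and the reading that inadequate images include index images. Overstatement is relative to all eligible men, not an error in an estimate declared to cover readable scans only. For assumed failure rates of 5% to 20% it is 1 to 4 points.

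The absence of any allowance in the sample size is a fact of the plan's own arithmetic, but it is the lesser part. The weightier part is who is counted.

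**What to change.** - Drop inadequate index images as a ground for withdrawal, and keep every Likert 3 or 4 man with mpMRI and histology.
- In the primary false-positive comparison, count an unreadable index test as index-positive, separately for VERDICT and LWI, so that failure of one does not affect the other.
- Have the radiologist already blinded under Data analysis record adequacy for each test.
- Report the number of failures per test, and show the readable-only result as a sensitivity analysis.
- For true positives and sensitivity, show results with and without the failures, so that an unreadable scan is not credited as a detection.
- Restate power for an assumed, justified failure rate, whether men are kept or withdrawn.

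If withdrawal is retained, state which images trigger it, whether it applies per test, and that the estimate covers readable scans only.

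The cost is protocol wording and some added analyses, with no new procedures. The reported fall becomes less favourable, and so does the stated power if the independent-groups formula is kept: holding 90% on that formula would need more men.
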